#### Imaging

In order to carefully determine the EZ and all possible (a)symptomatic side effects, magnetic resonance imaging (MRI) will be performed for all patients before and 2 years after inclusion. The patients in the waitlist-control arm which are treated with SRT will also receive a post-treatment MRI, 4 years after inclusion (= 2 years after SRT). The MRI protocol includes T1, T2, and susceptibility weighted imaging, fluid-attenuated inversion recovery (FLAIR), inversion recovery pulse sequence (cs IR), diffusion tensor imaging (DTI), and functional MR imaging.

#### Cognitive evaluation

In order to determine possible side effects on cognitive functioning, an evaluation will be performed for all patients before and 2 years after inclusion. The patients in the waitlist-control arm which are treated with SRT will be planned for an evaluation 4 years after inclusion (= 2 years after SRT). Cognitive evaluation includes the Rey Auditory Verbal Learning Test (RAVLT [25]), Trail Making Test A and B (TMT-A; TMT-B [26]), Stroop test [27], Digit Span WAIS-IV [28], Dutch Reading Test for Adults (NLV, [29]), Fluency test (GIT [30]), and Letter Digit Substitution Test (LDST [31].

#### Quality of life

To evaluate the experienced quality of life, patients are asked to fill in questionnaires at baseline and on a yearly basis in the follow-up. Included are the EQ-5D-5L [32], AQOL-8D [33], QOLIE-31 [34], Cognitive Failure Questionnaire (CFQ [35]), and the Multidimensional Fatigue index (MFI [36]).

#### Cost-effectiveness

To be able to perform a cost-effectiveness analysis, questionnaires regarding healthcare utilization and resource use (iPCQ, iMCQ, iVICQ) will have to be completed yearly, by the patient (iPCQ, iMCQ) and the informal care giver (iVICQ).

#### Visual examination

Visual field examination will only be performed if the (to be treated) EZ is in the proximity of the visual pathway.

If there is missing information (e.g., missed appointments, questionnaires or diary information), the trial assistant will contact the patient.

### Study parameters and endpoints

The main study endpoint of this study is the reduction of seizure frequency in patients with focal DRE, resulting in a higher proportion of patients who show an improvement of at least 75% (radiotherapy-adapted Engel classification I–III) at 2 years. Secondary study endpoints are to assess the quality of life (QoL) after SRT, define safety, evaluate (serious) adverse effects, ASM use, and tolerability of SRT, and investigate the cost-effectiveness (CEA) of SRT compared to standard of care, neurocognitive, and MR imaging changes after treatment.

### Data management

Study administration and management will be performed by the trial coordinators who work at the Clinical Trial Office (CTO) Maastro. These trial coordinators will have access to the source data and the subject files and will be responsible for the archiving of all items that are necessary for reviewing the data of the study and ensuring quality control. Castor EDC will be used for the randomization, study database, and electronic questionnaires. Randomization will be based on the validated variable block randomization model within Castor EDC by the trial coordinator. A code will be attributed to each patient registered in the trial consisting of a sequential inclusion number with 3 digits and/or letters. This code will identify the patient and must be included on all case report forms. The code will be attributed by CTO and linked to the patient in a list kept by Clinical Trial Office Maastro only. This list can be viewed by the local researcher, monitor, and, if necessary, the IGJ (Inspectie GezondheidsZorg en Jeugd). The duration of the storage of study and imaging data at Maastro is 15 years. Monitoring will be done in compliance with the NFU (Netherlands Federation of University Medical Centres) Guidelines and based on “risk-based monitoring.” The monitoring will be performed by qualified monitors of Clinical Trial Office (CTO) of Maastro.

Premature termination of the study can occur when (1) the judgment of the competent METC that assessed the research is irrevocably withdrawn; (2) it appears that the continuation of the research cannot serve a scientific purpose, and this is confirmed by the METC that has given a positive assessment of the research; (3) the principal investigators are no longer able to perform the duties of principal investigator, and no substitute can be found by mutual consent; and (4) the DSMB recommends this.

### Statistical analysis

Analysis for the primary endpoint will be based on the intention-to-treat principle. Comparison between the SRT and standard of care group will be performed with a two-sided *Z*-test for proportions with significance level alpha 0.05. For this purpose, the proportion of patients reaching RAEC I–III per treatment group will be calculated and compared. Furthermore, the difference in proportions between groups will be determined and presented with the corresponding 95% confidence interval.

Statistical analysis for secondary endpoints will depend on the type of data and comparison. Differences between treatment and waitlist-control group are central to the analysis and will be presented as effect size and 95% confidence intervals. For categorical data, comparisons will be made using chi-square tests. Data from continuous variables will be checked for Gaussian distribution. Comparison of continuous variables of Gaussian-distributed groups will be performed using the independent samples *t*-test; for non-parametric analyses, the Mann–Whitney test will be adopted.

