## Background

Epilepsy has an incidence of around ~ 200,000 patients in the Netherlands and is a great burden to many patients due to the unpredictability of the seizures, a low quality of life, and the increased mortality rate in patients with epilepsy [1–4]. The population of interest for this trial is the group of patients with chronic and focal (= localization related) drug-resistant epilepsy (DRE) who are not eligible for, or do not want to undergo, open resective surgery. In the Netherlands, patients are selected for epilepsy surgery after discussion in a multidisciplinary team in three regional epilepsy surgery working groups connected to three university hospitals (UMC Utrecht, Amsterdam UMC, Maastricht UMC +) resulting in a total of approximately 200–250 surgeries per year [5]. The postoperative seizure freedom rates (= curation) vary between 60 and 90% with epileptogenic lesions on MRI and lesion type as major predictive factors [6]. It is estimated that about 140–150 patients/year within the Netherlands with a suspected focal origin of seizures cannot be offered open surgery and will receive the indication for palliative treatment (deep brain or vagus nerve stimulation (DBS or VNS) and chronic anti-seizure medication (ASM). Seizures and chronic use of ASM cause different somatic and mental side effects and bring also psychosocial consequences, e.g., feelings of dependence, anxiety, depression, and stigma, each impacting patients’ quality of life. Furthermore, the associated yearly healthcare costs for society are expected to be more than the 2004 estimate of €9500 per patient [7–9].

In the PRECISION trial, adult patients with focal DRE, not eligible for surgery, are offered non-invasive linear accelerator (LINAC)-based stereotactic radiotherapy (SRT) with curative intent. SRT has been used to treat several types of neoplasms in the brain for several decades. LINAC-based SRT refers to delivering the dose in one or several treatment sessions. SRT has been proven safe and effective for high-precision radiation treatment of small target volumes, e.g., brain metastases, benign tumors such as meningioma, pituitary adenoma, and vestibular schwannoma, in particular for those locations not easily accessible for surgery [10, 11].

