### Sample size calculation

Participants will be randomized between SRT and standard of care at a ratio of 1:1. We expect that 50% of the patients in the SRT group will reach RAEC I–III after 2-year follow-up compared to at best 15% in the standard of care group [17, 18]. Sample size calculation is based on a two-sided *Z*-test for proportions with pooled variance and continuity correction. Significance level alpha is set at 0.05 and power at 0.90. Dropout is set at 10%. A total number of 84 patients is needed for the analysis, randomized equally to the SRT group and the standard of care group. After correction for drop-out, the total number of patients becomes 94, with 47 patients randomized to each treatment arm.

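### The primary Z-test is valid but unadjusted, so baseline MRI and seizure frequency, already collected on every patient, are not used for precision or against chance imbalance

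*Protocol article*

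**What the plan says.** Under Statistical analysis, the primary comparison "will be performed with a two-sided *Z*-test for proportions with significance level alpha 0.05", by intention to treat: "the proportion of patients reaching RAEC I–III per treatment group will be calculated and compared". The difference in proportions is reported with a 95% confidence interval. No covariate is named.

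Under Data management, "Randomization will be based on the validated variable block randomization model within Castor EDC". No stratification factor is given.

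Two candidate baseline factors are available for everyone. Under Imaging, "magnetic resonance imaging (MRI) will be performed for all patients before and 2 years after inclusion". Table 1 marks seizure frequency at the pre-SRT visit.

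The Background names "epileptogenic lesions on MRI and lesion type as major predictive factors", but the subject of that sentence is seizure freedom after open surgery.

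The sample size rests on the same unadjusted comparison. "Sample size calculation is based on a two-sided *Z*-test for proportions with pooled variance and continuity correction"; the assumed rates are: "50% of the patients in the SRT group will reach RAEC I–III after 2-year follow-up compared to at best 15% in the standard of care"; and "Significance level alpha is set at 0.05 and power at 0.90".

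**The concern.** With about 42 evaluable patients per arm, neither the allocation nor the analysis, as the article describes them, protects against a chance imbalance in a factor that influences the outcome. If such a factor exists, the crude difference can move by several points in either direction, and adjustment would recover some precision from the same patients.

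MRI lesion status is a plausible candidate. SRT, like surgery, targets the epileptogenic zone. The inclusion criteria accept either MRI or SEEG evidence of the target, so patients with and without a visible lesion can both enter. Seizure frequency is the reference for the 75% reduction, but that does not by itself give every patient the same chance of reaching it.

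**Working it through.** **1. The plan's own figure.** Inputs from Sample size calculation: p1 = 0.50, p0 = 0.15, two-sided alpha 0.05, power 0.90, dropout 10%.

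- Pooled rate (0.50 + 0.15)/2 = 0.325.
- Uncorrected n per arm = [1.96·√(2·0.325·0.675) + 1.2816·√(0.25 + 0.1275)]² / 0.35² = 35.5.
- Continuity-corrected n = (35.5/4)·[1 + √(1 + 4/(35.5·0.35))]² = 41.02, so 42 per arm, 84 in total.
- 84/0.9 = 93.3, so 94, or 47 per arm. Both stated totals reproduce.

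**2. Power of the planned test at 42 per arm.**

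- Without continuity correction: Φ[(0.35 − 1.96·0.1022)/0.0948] = Φ(1.58) = 0.943. Simulation gives about 0.945.
- If the test itself is continuity corrected: about 0.91.

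Either way the stated 0.90 is met.

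**3. Gain from adjustment.** The documents give no predictor strength for this endpoint, so the odds ratios and prevalences below are assumptions. Cochran-Mantel-Haenszel test stratified by one binary factor, prevalence 50% or 70%, marginal rates held at 50% and 15%, 60,000 runs per setting:

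| Assumed odds ratio | Crude | Stratified |
|---|---|---|
| 1 | 0.946 | 0.943 |
| 2 | 0.945–0.947 | 0.946–0.948 |
| 3 | 0.946–0.947 | 0.950–0.954 |
| 6 | 0.945–0.946 | 0.959–0.967 |
| 10 | 0.946 | 0.966–0.976 |

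Cross-check: a factor explaining a share R² of outcome variance multiplies the variance by 1 − R². For R² of 5% to 15%, 84·0.95 = 80 and 84·0.85 = 71, so adjustment is worth about 4 to 13 patients.

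**4. A 20% control rate.** Comparison to anti-seizure medication gives 10% seizure free plus a further 10% with more than 75% improvement, over a median of 4 years. At 50% v 20% the crude test has power of about 0.84–0.85; adjusted analyses give 0.84–0.90. The top comes from logistic standardisation with an assumed lesion odds ratio of 4 and an odds ratio of 0.5 per SD of log seizure frequency, and it includes some of the type I inflation shown in step 6.

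**5. Chance imbalance.** For a 50% factor, the SD of the between-arm difference is √(2·0.25/42) = 0.109. A difference of 20 points or more has probability 6.7% by normal approximation and 6.3% by binomial simulation.

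At an assumed odds ratio of 6, the lesion and non-lesion rates would be 71% and 29% when the arm's rate is 50%, and 24.8% and 5.2% when it is 15%. A 20-point imbalance, 10 points in each arm, shifts the crude difference by 0.10·0.42 + 0.10·0.196 = 0.062. That is about 6 points against a planned 35.

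**6. Type I error of the alternatives, 42 per arm, 5,000 runs.**

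- Crude: 4.9–5.6%.
- Logistic standardisation with an uncorrected influence-function standard error: 6.2–6.7%.
- Lesion-stratified Mantel-Haenszel: 4.7–5.4%.

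So part of the apparent gain from uncorrected standardisation is a liberal standard error.

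**The case against.** The strongest reply is that nothing here is wrong. Under 1:1 randomisation the crude difference is unbiased, its confidence interval already allows for chance imbalance, and the analysis matches the sample size. That stands in full. A reader might infer that the unadjusted test is invalid or that the trial is underpowered because of it. The documents support neither: the totals reproduce, and the planned test exceeds 0.90 at the protocol's own rates.

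A reader might also infer that the protocol itself treats lesion status as a major predictor of this trial's outcome. It does not. The statement concerns seizure freedom after open surgery, while this trial enrols patients not eligible for surgery and counts a reduction of at least 75%. Nor is baseline seizure frequency called prognostic anywhere. The relevance of both is plausible but assumed.

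The plan expects few responders, about 21 + 6 = 27 among 84, which limits the number of covariates and makes large-sample standard errors optimistic. That also stands, and it governs the choice of method.

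Lastly, a supportive adjusted analysis may be in the SAP, and strata may be in the full protocol; neither is shown. Their absence from the article is therefore no fault. What remains is that the article does fix the primary test as unadjusted, so an adjusted primary analysis would have to be a deliberate change.

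**Conclusion.** The point holds as an efficiency improvement. The primary analysis is valid but leaves unused precision and protection that the collected baseline data could provide.

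At 50% v 15% the gain is about 0 to 3 points of power (about 0.945 to 0.94–0.975). At a 20% control rate it is about 0 to 5 points (about 0.85 to 0.84–0.90). The low ends include a slight loss when the factor is not prognostic; the high ends need strong predictors. An imbalance of 20 points or more in a 50% factor would occur in about 6% of randomisations. All sizes rest on assumed prevalences and odds ratios and on 42 evaluable patients per arm.

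**What to change.** In Statistical analysis, keep the difference in proportions as the estimand and prespecify adjustment for at most two baseline factors: MRI lesion (yes/no) and log baseline seizure frequency. Choose one method in advance:

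- a Mantel-Haenszel risk difference with the Cochran-Mantel-Haenszel test, stratified by lesion status; or
- standardisation from a logistic model with treatment and both factors, with a small-sample-corrected standard error or a permutation test.

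Do not use the uncorrected influence-function standard error at this sample size. Report the crude Z-test as a sensitivity analysis.

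The cost is one paragraph, with no new data or patients. Covariates and method must be fixed before outcomes are examined by arm. The stratified test loses up to about 1 point of power if lesion status turns out not to be prognostic.

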#### Quality of life (QoL)

*Quality of life (QoL)* after SRT will be calculated from the corresponding questionnaires. According to the respective scoring manuals, subscale and total scores will be calculated. Descriptive statistics for these continuous variables will be presented as described above, and comparisons between treatment groups at specific timepoints will be made.

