#### Neurocognition

For neuro-cognitive test variables, the Reliable Change Index (RCI) will be calculated by dividing the difference between pre-treatment (baseline) and posttreatment (2 year) scores by the standard error of the difference. The standard error of the difference will be defined based on the reference data from literature for each test. A RCI > 1.5 will be used to quantify as significant change. Differences in RCI between treatment and waitlist-control group will be compared and presented as effect size and 95% confidence interval.

A loss of follow-up is taken into account for 5 patients in each treatment arm. If patients withdraw from the study, patients will be referred back to the treating physician. Data collected until the time of withdrawal will be used for analysis, unless the patient decided his data must be destroyed.

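### Quality-of-life scores are to be compared between arms at single timepoints without the baseline scores the trial collects: valid, but less precise than the same data allow

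*Protocol article*

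**What the plan says.** The Statistical analysis section of the protocol article sets a general rule for continuous secondary variables. After a check for a Gaussian distribution, "Comparison of continuous variables of Gaussian-distributed groups will be performed using the independent samples" *t*-test; otherwise, "for non-parametric analyses, the Mann–Whitney test will be adopted". Group differences "will be presented as effect size and 95% confidence intervals".

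The Quality of life (QoL) paragraph under that section refers back to this rule and says that "comparisons between treatment groups at specific timepoints will be made". It names no change score, baseline covariate or repeated-measures model.

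Baseline scores are nevertheless collected. Under Study procedures, the Quality of life paragraph says that "patients are asked to fill in questionnaires at baseline and on a yearly basis in the follow-up", and Table 1 shows the questionnaires before SRT and at every yearly visit.

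Neurocognition is handled differently. The Reliable Change Index (RCI) is obtained by "dividing the difference between pre-treatment (baseline) and posttreatment (2 year) scores by the standard error of the difference", and "Differences in RCI between treatment and waitlist-control group will be compared and presented as effect size and 95% confidence interval".

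**The concern.** A patient's quality of life two years after randomization depends in part on where that patient started. A *t*-test or Mann–Whitney test on the 2-year score alone leaves this predictable part in the error term. With about 42 patients per arm, the interval is then wider than it needs to be, and a chance difference between the arms at baseline passes into the point estimate uncorrected.

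Two features of the stated rule add to this. First, choosing the test by a normality check lets the estimated quantity change from a mean difference to a rank comparison between scales, or between visits of one scale. Second, the Mann–Whitney test does not by itself give the effect size and 95% confidence interval that the same section promises.

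Quality of life is a named secondary objective, and the Discussion says that side effects will be weighed against the anticipated gain in quality of life. That judgement depends on how precisely the gain is estimated.

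**Working it through.** **1. Number per arm.** The Sample size calculation section expects that "50% of the patients in the SRT group will reach RAEC I–III after 2-year follow-up compared to at best 15" per cent, with two-sided alpha 0.05, power 0.90, pooled variance and a continuity correction.

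- Without correction: n = [1.96·√(2·0.325·0.675) + 1.2816·√(0.25 + 0.1275)]² / 0.35² = 35.5, so 36 per arm.
- With correction: (35.5/4)·[1 + √(1 + 4/(35.5·0.35))]² = 41.0, so 42 per arm and 84 in total.
- With 10% dropout: 84/0.9 = 93.3, so 94.

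This reproduces the article's 84 and 94. The article gives no power figure for quality of life, so n = 42 per arm is carried over as the number analysed.

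**2. Effect of baseline adjustment.** Rho is the within-arm correlation between the baseline and 2-year scores. The article does not give it, so a range is assumed. In units of the SD of the 2-year score:

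- Variance of the unadjusted difference: 2/42, so SE = 0.218.
- Variance with baseline as covariate: (2/42)·(1 − rho²).
- Difference detectable with 80% power: (1.96 + 0.8416)·√[(2/42)(1 − rho²)].
- Power for an assumed difference of 0.5 SD: Φ(0.5/√[(2/42)(1 − rho²)] − 1.96).

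| Assumed rho | Variance ratio 1 − rho² | Detectable difference (SD) | Power for 0.5 SD | Unadjusted n per arm giving the same precision |
|---|---|---|---|---|
| unadjusted | 1.00 | 0.61 | 63% | 42 |
| 0.3 | 0.91 | 0.58 | 67% | 46 |
| 0.5 | 0.75 | 0.53 | 75% | 56 |
| 0.6 | 0.64 | 0.49 | 82% | 66 |
| 0.7 | 0.51 | 0.44 | 89% | 82 |

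The last column is 42/(1 − rho²). A simulation with 4,000 runs per rho, normal data and a 0.5 SD difference agrees. Power was 0.61 to 0.62 for the *t*-test and about 0.60 for Mann–Whitney, against 0.65, 0.74 and 0.88 for ANCOVA at rho 0.3, 0.5 and 0.7.

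**3. Chance imbalance.** The SE of a baseline difference is also 0.218 SD. A gap of more than 0.3 SD in either direction has probability 2·[1 − Φ(0.3/0.218)] = 17% for any one scale. At rho 0.6, a 0.3 SD gap moves the unadjusted estimate by 0.6·0.3 = 0.18 SD.

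**4. Cognition.** The standard error in the RCI comes from reference data, so the RCI is a rescaled change score. Compared as a continuous score, its variance is 2(1 − rho) relative to the 2-year score. The ratio of ANCOVA to change-score variance is (1 − rho²)/[2(1 − rho)] = (1 + rho)/2.

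| Assumed rho | Variance ratio (1 + rho)/2 | Detectable difference, change score (SD) | Detectable difference, ANCOVA (SD) |
|---|---|---|---|
| 0.3 | 0.65 | 0.72 | 0.58 |
| 0.5 | 0.75 | 0.61 | 0.53 |
| 0.6 | 0.80 | 0.55 | 0.49 |
| 0.7 | 0.85 | 0.47 | 0.44 |

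At rho 0.6 and 0.7, ANCOVA intervals would be narrower by 1 − √0.80 = 11% and 1 − √0.85 = 8%. Below rho 0.5, the change score is less precise than the 2-year score alone.

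**The case against.** The strongest defence is that the planned test is valid. In a randomized comparison the unadjusted difference is unbiased, its type I error is correct, and its confidence interval already allows for chance imbalance at baseline. These are secondary outcomes with no stated power target. All of this stands: the point concerns efficiency, not validity.

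The size of the gain rests on an assumed rho. The interval is two years, and the treatment is expected to change seizure status in many patients of one arm, so a high correlation cannot be taken for granted. This also stands, which is why the range starts at 0.3, where the gain is small. Adjustment still costs only one degree of freedom there.

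The article condenses a fuller protocol and says that secondary analyses depend on the type of data and comparison, so it does not expressly exclude change scores or adjusted models. But it does name the tests and does say that arms are compared at specific timepoints. That is a stated choice, not a silence to be filled by the analysis plan. If change scores were meant, the (1 + rho)/2 ratio above shows that ANCOVA would still be at least as precise.

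A reader might infer that all continuous secondary outcomes ignore baseline, or that the question of cognitive harm will be answered with far wider intervals than necessary. The article does not support this. Cognition uses baseline through the RCI; adverse effects, medication use and tolerability are classed as categorical; cost-effectiveness is modelled. Nor does a yearly schedule show that every patient will supply a baseline score. That the article names no stratification factor is no part of this point.

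**Conclusion.** The point holds for the quality-of-life questionnaires. The stated analysis leaves out the baseline score and so gives up a fraction rho² of the attainable precision: 9% at rho 0.3, 25% at 0.5, 36% at 0.6 and 49% at 0.7. To call this a large loss is justified only if rho is about 0.5 or more, which the article neither states nor rules out. The figures assume 42 analysed per arm, equal variances, a linear relation to baseline and complete baseline scores.

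The gap between the Mann–Whitney test and the promised effect size with confidence interval does not depend on rho.

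For cognition, the gain from ANCOVA over the RCI is modest at rho 0.6 to 0.7, worth 1/0.80 = 1.25 to 1/0.85 = 1.18 times the sample size. The factors of about 1.6 to 2.0 that apply to quality of life at the same rho (1/0.64 and 1/0.51) must not be carried over. Nothing here touches the primary endpoint or the sample size of 84 and 94.

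**What to change.** Analyse each quality-of-life score with a linear mixed model on the 1- and 2-year values, with arm, time, arm-by-time interaction and the baseline score as terms. ANCOVA on the 2-year score with baseline as covariate is a simpler alternative. Report the adjusted mean difference at 2 years with its 95% confidence interval for every scale. Drop the choice of test by normality check, and use robust or bootstrap intervals for skewed scales.

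The mixed model has a further advantage. The Neurocognition section allows for five losses per arm and says that data up to withdrawal will be used. A 2-year *t*-test cannot use the 1-year score of a patient who leaves after that visit; the mixed model can.

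For cognition, ANCOVA on the 2-year test score could be reported beside the RCI, as an optional refinement.

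The cost is analysis wording only, with no new data, visits or patients. The change should be made before outcome data are examined by arm. If the full protocol or analysis plan already adjusts for baseline, it is enough to record that the article's wording is superseded.
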